### Diagnostic part

An important part of the diagnostic procedure in this study is founded on manual examination of the muscles and joints. Palpation used as a diagnostic tool for spinal dysfunction has been subjected to criticism because of poor reproducibility and validity [38]. One of the major problems with the validation of palpation is that there is no golden standard to directly validate the findings. In the present study, this problem is addressed by using MPS as a *by proxy *measure to indirectly validate the CTA diagnosis. This is based on the hypothesis that in this population, patients who are CTA positive most likely will have fewer abnormal MPS than CTA negative patients. Data from the pilot study suggest that approximately 40% are CTA-positive, 15% have abnormal MPS, and 7% have both abnormal MPS and are CTA positive.

### Outcome measures

We have chosen global perceived effect as one out of two primary outcome measures even though critique has been posted on the reliability and validity of global rating scales [39]. Global rating scales are typically correlated with the patients' present status and are not an unbiased measure of change. However, global rating scales are regarded as clinically relevant and valid, and responsive to measure patients' perceived recovery. The global rating scale was also chosen, because during the pilot study we found that pain intensity levels were relatively low compared to for instance patients seeking care for low back pain. Patients initially reported very high levels of pain which then spontaneous decline in intensity within a very short period of time (hours to days), rendering pain a less than optimal primary outcome measure. Finally, we found that the Patient Specific Functional Scale [33] would not make a good primary outcome measure because many patients experience a first time episode of chest pain and, thus, do not feel limited in their daily activities.

### Interventions

Chiropractic therapy may be an effective treatment for patients with acute chest pain, but this has only been investigated in one non-randomized trial [27]. A pragmatic approach was chosen for the therapy group. The exact content of chiropractic therapy may not be clear, and the potential active "ingredient" can not be known even after this trial is completed. The advantage of the pragmatic strategy is that if this trial provides evidence in favor of chiropractic therapy, the results can easily be implemented, but future trials will be needed in order to identify the specific components. Also, our design is not well suited to correct for attention bias. Advice was chosen as intervention for the second group, because it is intended to mimic usual care and will act as a control treatment. Chiropractors are an integrate part of the Danish primary health care system with approximately 15% of Danes consulting a chiropractor each year [40]. Patients that previously have received chiropractic treatment very often have specific expectation about what chiropractic treatment consists of. This means that choosing a sham or placebo treatment was not feasible in Denmark due to lack of naïve patients, and because masking of patients to a sham or placebo treatment would not be possible.

In this study we have focused on two conditions that may cause episodes of chest pain, i.e. ischemic heart disease and CTA. Many other conditions may be present in these patients that could cause chest pain. Optimally, a thorough follow up, including evaluation of esophageal-gastro-intestinal conditions, would have been preferable to potentially diagnose some of the CTA-negative patients, but due to limitations in funding and time restraints such evaluation has not been possible.

In summary, this article presents the rationale and design of a multi-purpose study consisting of a prospective diagnostic study, and an RCT, with a cost-effectiveness study alongside the central trial. It is anticipated to be completed in 2008, at which time the results will be made available. The first part of this study may potentially demonstrate that a chiropractor is able to identify a subset of patients suffering from chest pain predominantly of musculoskeletal origin among patients dismissed from an acute chest pain clinic with no apparent cardiac condition. The long term goal is to establish whether manual palpation may be used as a part of the clinical examination to screen patients allowing for improvement in referral patterns. Furthermore knowledge about the benefits of manual treatment in patients with musculoskeletal chest pain will inform clinical decision and policy development in relation to clinical practice.

## Appendix 1

### Myocardial Perfusion Scintigraphy (MPS)

All patients undergo an electrocardiographically gated rest MPS according to the rest part of a two-day protocol without attenuation correction [41]. ^99m^Tc-sestamibi (10 MBq. kg^-1^, maximum 1100 MBq) is given 20 min. after sublingual administration of 0.5 mg nitro-glycerine followed 30–60 min. later by imaging using a dual-head gamma camera. A semi-automatic quantitative interpretation of perfusion and functional data is carried out using standard processing software (Auto QUANT^® ^5.0.0) [42]. Abnormal segmental perfusion scores is computed in a 20-segment model using a 5-point perfusion scoring scale (0 = normal, 1 = equivocal, 2 = moderate, 3 = severe reduction of radioactivity, and 4 = absence of detectable tracer uptake in a segment based on a normal databases set up for each sex). The summed rest score (SRS) is obtained by adding the scores of each segment in the 20-segment model [43]. A study is judged abnormal if the sum of stress scores is = 4 with at least one segment having a score = 2. In case of an abnormal MPS at rest, additional stress imaging is carried out at least two days later using adenosine infusion 0.140 mg. kg^-1. ^min^-1 ^for six minutes and injection of 10 MBq. kg^-1 ^(maximum 1100 MBq) of sestamibi between the third and the fourth minute of infusion. Similarly, from the images, the summed rest score (SRS) is calculated [43]. All studies are interpreted without knowledge of the clinical findings. In patients with both rest and stress images the type of abnormality is categorized as follows: Defects that are present at rest and remains unchanged during stress are considered as fixed. The appearance of new or worsening defects following stress is considered to be defect reversibility. Studies combining fixed and reversible defects are categorized as "reversible". The diagnostic accuracy of the MPS method has been reported elsewhere, and the estimated sensitivity and specificity for detecting significant coronary disease is 75% (95% CI 66%–82%) and 79% (95% CI 73%–84%), respectively [44].

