An extensive body of literature addresses patient assessment and management protocols for patients presenting with chest pain, but these focus primarily on cardiopulmonary [19-22], gastro-oesophageal [5,23], and psychological conditions [11,24,25], and protocols aiming at diagnosis of musculoskeletal chest pain remain scarce, and the effect of treatment strategies, including medical treatment (oral anti-inflammatory drugs), exercise (strength and/or stretching), advice, and manual approaches have not been evaluated. To our knowledge, only one non-randomized study deals with manual examination and treatment of patients with musculoskeletal chest pain [26,27]. In this study, an examination program consisting of a general health examination and a specific manual examination of the thorax and cervico-thoracic part of the spine was developed for a population of patients with suspected or known stable angina pectoris referred to a tertiary hospital for coronary angiography [26]. The examination program together with the detailed case history was applied by a chiropractor to make a diagnosis of discomfort from the musculoskeletal system, cervico-thoracic angina (CTA). In the absence of a true golden standard to validate the CTA diagnosis, myocardial perfusion scintigraphy (MPS) was used as a *by proxy *measure of validity with some success: Eighty percent of the CTA-positive patients had normal perfusion compared to 50% in the CTA-negative group. Moreover, results indicated that patients with CTA may benefit from chiropractic treatment.

We therefore decided to perform a multi-purpose clinical trial consisting of 1) a prospective, population-based, diagnostic evaluation study, 2) a single-blinded, randomized clinical trial (RCT), and 3) a cost-effectiveness analysis alongside the RCT.

The aims are:

• To determine the proportion of patients discharged from a university hospital chest pain clinic in whom their chest pain may be of musculoskeletal rather than cardiac origin. Specifically, we wish to determine the prevalence and character of musculoskeletal chest pain, and to describe cardiac status with respect to ischemic heart disease.

• To investigate the diagnostic decision making process of a chiropractor in these patients, using MPS as an indirect measure of validity.

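### The scintigraphy abnormality rule is written on stress scores that most patients will not have, and a normal scan means only normal perfusion at rest

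*Protocol article*

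**What the plan says.** Appendix 1 of the protocol article starts with one scan for everyone: "All patients undergo an electrocardiographically gated rest MPS according to the rest part of a two-day protocol without attenuation correction". It defines a summed rest score over 20 segments and then gives its only criterion for an abnormal study: "A study is judged abnormal if the sum of stress scores is = 4 with at least one segment having a score = 2". (The equals signs may be comparison signs lost when the PDF was read. Nothing here depends on them.) The next sentence sets the condition for a second scan: "In case of an abnormal MPS at rest, additional stress imaging is carried out at least two days later". Of those later stress images it says: "Similarly, from the images, the summed rest score (SRS) is calculated". No summed stress score is defined anywhere.

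For patients who have both scans, the appendix separates fixed from reversible findings: "The appearance of new or worsening defects following stress is considered to be defect reversibility". It closes with a sensitivity of 75% (95% CI 66% to 82%) and a specificity of 79% (73% to 84%), taken from a cited source.

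The result is used in three places. One of the aims in the Background is "to describe cardiac status with respect to ischemic heart disease", and the MPS section in Methods gives the same purpose. Data analyses (Diagnostic study) splits patients by normal or abnormal MPS and compares the proportion who are CTA positive. The Discussion (Diagnostic part) presents MPS as the proxy by which CTA is indirectly validated, and reports that about 15% of pilot patients had an abnormal MPS.

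**The concern.** There are two separate difficulties.

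The first is that the text contradicts itself. A decision that must be made on the rest scan is defined by a score that comes from a scan not yet done. For a patient whose rest scan is read as normal, that score never comes to exist. The stress scan, in turn, is given the rest scan's label. This rule creates the grouping variable for the CTA comparison, so two readers could not be sure of applying the same one.

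The second remains after the wording is corrected. The appendix recognises defects that are new on stress, but a patient with normal rest perfusion never has the scan that could show one. Such patients are counted as having a normal MPS by design. The article does not say so. Its Discussion acknowledges that gastrointestinal causes were not investigated, but not this gap. The risk is that a normal result is reported as absence of ischaemic heart disease, and that some patients with stress-only defects sit in the reference group for validating CTA.

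**Working it through.** The article states no sample size or power for the MPS comparison, so there is no planned figure to reproduce. The check is a reading of the sequence followed by simple arithmetic.

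**Sequence, taken literally**

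| Step | Score available | Score the rule needs |
|---|---|---|
| Rest scan, all patients | summed rest score | sum of stress scores |
| Decision on stress imaging | summed rest score | sum of stress scores |
| Stress scan, rest-abnormal patients only | stress segment scores, labelled summed rest score | sum of stress scores |
| Final class, rest-normal patients | summed rest score | sum of stress scores |

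The required score exists only in the third row.

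**How many patients have no stress score**

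Inputs: 300 patients (Study population); about 15% abnormal MPS in the pilot (Discussion, Diagnostic part); pilot of 36 patients (Discussion). Assumptions: the 15% is the rate at the rest scan, and all 36 pilot patients were scanned.

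- Stress imaging: 300 × 0.15 = 45.
- No stress imaging: 300 × 0.85 = 255 (85%).
- 15% of 36 is 5.4, so 5 or 6 patients. Exact (Clopper-Pearson) 95% intervals are 4.7% to 29.5% for 5/36 and 6.4% to 32.8% for 6/36.
- Over both, the share without stress imaging runs from 1 − 0.328 = 67% to 1 − 0.047 = 95%, or about 202 to 286 of 300.

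Most patients lack a stress score across the whole range.

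**How many could be misclassified**

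The documents give no rate of stress-only defects. Let *f* be that rate among the 255 (assumed range 2% to 15%):

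| *f* | 255 × *f* |
|---|---|
| 2% | 5 |
| 5% | 13 |
| 10% | 26 |
| 15% | 38 |

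**Effect on the CTA comparison**

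Assume that the abnormal group is correctly classified and that patients with stress-only defects are CTA positive as often as that group (proportion *a*). With proportion *b* in the truly normal, the observed proportion in the MPS-normal group is (1 − *f*)*b* + *fa*. The observed difference is then *a* − [(1 − *f*)*b* + *fa*] = (1 − *f*)(*a* − *b*). The contrast shrinks by the fraction *f*, that is by 2% to 15% of its true size over the assumed range. Under these assumptions the bias is towards no difference.

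**The case against.** The strongest reply is that the contradiction is a one-word slip. The rule follows directly on the definition of the summed rest score and precedes the sentence about an abnormal rest scan, so *stress* probably should read *rest*. That is plausible, and it would resolve the first difficulty. The text still needs correcting because the rule defines an analysis variable, and the second difficulty is untouched.

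It is also fair to say that little else hangs on MPS. CTA is diagnosed from history and examination at baseline, before the scan. The aim says only that pain may be musculoskeletal, and MPS is repeatedly described as an indirect measure. Entry to the randomised trial, its outcomes and its sample size do not use it. Scans are read without knowledge of the clinical findings, which supports dilution rather than spurious agreement. All of this stands and confines the point to the diagnostic part.

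A reader might go further and infer that the quoted accuracy cannot apply here. A specificity of 79% implies at least 21% positive scans, and 15% positive gives a prevalence of (0.15 − 0.21)/(0.75 + 0.79 − 1) = −11%. At the upper confidence limits, 82% and 84%, it is (0.15 − 0.16)/(0.82 + 0.84 − 1) = −1.5%. The documents do not support that inference, because it treats an approximate pilot figure as exact. If 21% were the true rate, 5 or fewer positives in 36 would occur with probability 0.20, and 6 or fewer with probability 0.34. Putting the upper limits of 29.5% and 32.8% into the same formula at 75%/79% gives prevalences of about +16% and +22%. The source of the accuracy figures is not shown, so neither its imaging sequence nor its population can be compared. What can be said is that the article does not show that the figures apply to a sequence in which stress imaging depends on the rest scan.

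**Conclusion.** The point holds for the diagnostic part. Appendix 1 is wrong as written: its abnormality rule cannot be applied at the decision it governs, nor to any patient with a normal rest scan. The size, about 255 of 300 (about 202 to 286), rests on taking the pilot rate as the rate at the rest scan, which the article does not say.

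Independently of that wording, a normal MPS under this sequence establishes normal resting perfusion and no more. This limits what may be concluded about ischaemic heart disease in the cohort and probably weakens the CTA comparison. The number of patients affected cannot be derived from the documents. The 5 to 38 shown is a range under an assumed rate, and the direction of the bias depends on the stated assumptions. A reader might also infer that the randomised comparison is compromised. It is not, since nothing in it depends on MPS.

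**What to change.** Reconcile three items in Appendix 1 before the CTA comparison is run: the score on which abnormality is judged, the condition for stress imaging, and the names of the rest and stress scores. Which imaging sequence is right is for the investigators to settle.

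If stress imaging continues to depend on the rest scan:

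- call the classification used in all 300 patients *resting perfusion defect*, in the aims, the MPS section and the diagnostic analysis;
- report reversibility only among patients with an abnormal rest scan, with that denominator;
- state that a normal rest scan is not interpreted as absence of ischaemic heart disease, and that stress-only defects fall in the normal group of the CTA comparison;
- state that the quoted 75% and 79% are not shown to apply to this sequence.

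The cost is wording and a narrower diagnostic claim. No additional scans, patients or changes to the randomised trial are involved.
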